#### Ethics and dissemination

The study will be conducted according to the principles of the Declaration of Helsinki following GCP rules.

As stated in the current version of Fortaleza, Brazil, 2013 and in accordance with the Dutch Medical Research Involving Human Subjects Act (WMO).

The study protocol has been approved by the Amsterdam UMC (AMC) local Ethics Committee (NL63104.018.17 - METC 2017_225). The study has been registered at the Dutch Trial Register, ID: NTR6943.

#### Statistical analysis

Sample size was calculated using data from previous studies where BWSTT [12] and usual care [24] was provided to critically ill patients in the Amsterdam UMC. Data of 35 patients were retrieved. On average, these patients reached the endpoint (≥ FAC 3) at day 15 after the inclusion criteria were met. In the sample data, we found a hazard ratio of 1.87 at 15 days in favor of BWSTT. All patients reached the endpoint within the study period. Given a type 1 error rate of 5% and a power of 0.8 the analysis resulted in a required sample size of 88 (44 + 44) patients before correction for attrition, assuming a 10% dropout rate. A check on sample size assumptions will be performed after inclusion of 40 participants as the dataset used for sample size to calculate was relatively small.

The primary objective of this study is to assess the effect of BWSTT in critically ill patients on time to functional ambulation as compared to usual care. For this, Kaplan-Meier analyses will be performed and comparisons between both groups will be made. For the primary analysis we will use intention to treat principles. Multiple imputation will be applied in cases where the primary outcome is missing. Cox regression analysis will be performed when imbalances between groups are found at baseline in age (mean difference ≥ 10%), muscle strength (MRC sum-score mean difference ≥ 10%), functional ambulation level (FAC mean difference > 1) and co-morbidities (Charlson Comorbidity Index [CCI] mean difference > 1) as they are potentially related to the primary outcome. Significance values are not considered when determining baseline differences.

The secondary objective of this study is to analyze between group differences of other patient relevant outcome measures for the evaluation of BWSTT. Patient characteristics and secondary study endpoints will be described using descriptive statistics according to their distribution. If the variables are normally distributed, they are expressed as mean and standard deviation (SD). Skewed variables are presented with medians and interquartile ranges (IQR). Between groups comparisons will be made using the appropriate tests according the variable type and distribution.

For this study, analysis will be performed using the software package R version 3.6.1.

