#### Main study endpoint

The main study endpoint is the number of days to functional ambulation of 3 or higher as measured with the FAC. The FAC categorizes patients according to basic motor skills necessary for functional ambulation [21]. FAC categories are rated as follows:

(0) The patient cannot walk, or needs help from two or more persons, (1) the patient needs firm continuous support from one person who helps carrying weight and with balance, (2) the patient needs continuous or intermittent support of one person to help with balance and coordination, (3) the patient requires verbal supervision or stand-by help from one person without physical contact, (4) the patient can walk independently on level ground, but requires help on stairs, slopes, or uneven surfaces, (5) the patient can walk independently anywhere.

The FAC will be assessed daily until hospital discharge by a researcher blinded to the intervention. Should a patient still receive BWSTT after transfer to the regular ward, the study intervention, and the blinded outcome assessment will be performed separately. If a patient is discharged to another hospital before the main study endpoint (FAC 3) is reached, the assessment of walking capacity will be continued until a FAC score of 3 has been reached.

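### The missing-outcome rule and the Kaplan-Meier analysis make no exception for death before FAC 3, so the reported curve would overstate the share of patients who regain walking

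*Protocol article*

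**What the plan says.** The Main study endpoint section defines the outcome as a duration: "The main study endpoint is the number of days to functional ambulation of 3 or higher as measured with the FAC". FAC is assessed daily until hospital discharge. Patients who move to another hospital before FAC 3 are followed until they reach it.

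For the analysis, the Statistical analysis section states: "For this, Kaplan-Meier analyses will be performed and comparisons between both groups will be made". It adds intention to treat and one rule for missing data: "Multiple imputation will be applied in cases where the primary outcome is missing". It does not mention death before FAC 3 or competing events.

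Of the 35 planning patients the same section says: "All patients reached the endpoint within the study period". Death is nevertheless foreseen: the Adverse events section lists it among serious outcomes. The Exclusion criteria remove only patients whose death is imminent.

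**The concern.** A patient who dies before FAC 3 has no number of days to FAC 3 and never will. Read literally, the imputation rule would create a walking date for that patient. If deaths are instead censored in the Kaplan-Meier analysis, they are assumed to have gone on to walk at the same rate as those still under observation. Both routes lead to the same quantity: walking in a hypothetical population without deaths.

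Two things are at stake. First, the curve will be read as the share of patients who regain walking, and for that purpose it is too high. Second, if more patients die in one arm, a death-censored or imputed comparison does not show that fewer patients in that arm ever walk. This matters for a device without CE certification in a critically ill population, where a safety board watches for harm. The planning data contained no deaths before the endpoint, so they could not have exposed the problem.

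**Working it through.** **1. The plan's own figure.** Inputs from the Statistical analysis section: "Given a type 1 error rate of 5% and a power of 0.8", "we found a hazard ratio of 1.87 at 15 days in favor of BWSTT", "required sample size of 88 (44 + 44) patients before correction for attrition, assuming a 10% dropout rate". I assume a two-sided test; the article does not say. If every patient reaches FAC 3, the number of events equals the number of patients.

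- Freedman: (1.96 + 0.842)² × (2.87/0.87)² = 7.85 × 10.88 = 85.4, so 86 before attrition.
- Schoenfeld: 4 × 7.85 / (ln 1.87)² = 31.4 / 0.392 = 80.1, so 81. Dividing by 0.9 gives 90 after attrition.

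Both lie within 2 of 88, so the sample size reproduces and is not disputed here. Both calculations allow no deaths before FAC 3.

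**2. Effect on the curve.** The article gives an average of 15 days to FAC 3; I use it as a median (assumption). The share p who die before FAC 3 is not given, so I take 5% to 20% (assumption). Hazards are constant and the two event times are independent.

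- Walking hazard: λ = ln 2 / 15. Death hazard: μ = λp/(1 − p), so that a share p eventually dies first.
- Death censored or imputed: 1 − KM(t) = 1 − exp(−λt). At day 60 this is 1 − 2⁻⁴ = 0.938, whatever p is.
- Death as a competing event: CIF(t) = (1 − p)(1 − exp(−(λ + μ)t)). At day 60 this is (1 − p)(1 − 2^(−4/(1 − p))).

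| p | 1 − KM, day 60 | CIF, day 60 | Overstatement |
|---|---|---|---|
| 5% | 0.938 | 0.899 | 4 points |
| 10% | 0.938 | 0.859 | 8 points |
| 15% | 0.938 | 0.817 | 12 points |
| 20% | 0.938 | 0.775 | 16 points |

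Across the same range of p, the overstatement is 1 to 4 points at day 15 and 2 to 9 points at day 30.

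**3. Effect on the group comparison.** Simulation with 44 per arm, 3,000 runs and equal walking hazards. Three analyses were compared: log-rank with deaths censored, multiple imputation of FAC 3 times for the dead (10 imputations, exponential model by arm), and log-rank with the dead kept at risk as never walking. Rejections at the two-sided 5% level:

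| Deaths, control / BWSTT | Censored | Imputed | Dead kept at risk |
|---|---|---|---|
| 10% / 10% | 5.1% | 5.2% | 5.1% |
| 5% / 15% | 6.2% | 5.8% | 15.7% show BWSTT worse |
| 5% / 25% | 5.5% | 5.2% | 43.4% show BWSTT worse |

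Censoring and imputing both test the walking hazard and stay near 5% to 6%. Neither responds to the lower chance of walking in the arm with more deaths.

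**4. When deaths fall on slow recoverers.** An illustrative scenario assumes 30% frail patients (mean recovery 35 days against 10 for the rest), deaths only among the frail, no true effect on recovery, and 4% against 11% deaths. Depending on how death times are modelled, the death-censored hazard ratio is 1.04 to 1.06 in favour of BWSTT; with the dead kept at risk it is 0.89 to 0.92. With 44 per arm the standard error of the log hazard ratio is about 0.23, so ln 1.06 = 0.058 is about a quarter of one standard error.

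**The case against.** The strongest objection is that no sentence classes death as a missing outcome. Kaplan-Meier is the named method, so censoring deaths is at least as natural a reading as imputing them. The article also condenses a full protocol, and an analysis plan may exist. This stands in part: a reader might infer that the trial will impute walking dates for the dead, and the text does not establish that. But the article does state a rule without an exception, and the curve has the same meaning under either reading.

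Three stronger readings are tempting, and the documents do not support them.

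- **Patients who leave are mishandled in the same way.** Transferred patients are followed to FAC 3. Patients who withdraw or go home alive can still walk later, so imputing or censoring their time is an ordinary missing-data assumption. Discharge may be related to function, so simple censoring there is not clearly better than imputation.
- **The group comparison is wrong.** A death-censored hazard ratio is a legitimate estimand for time to ambulation, and its test stays near its nominal level in the simulations. Even the frail-subgroup scenario moves it little.
- **Gray's test or a Fine-Gray model must replace the primary comparison.** Those answer a question that mixes mortality with walking, and they carry a cost. With a true walking hazard ratio of 1.87 and 10% deaths in each arm, the death-censored log-rank detected the effect in 77% of simulated trials, against 33% with the dead kept at risk. In that simulation both curves end at the same plateau, so 33% illustrates the cost and is not a forecast.

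Deaths may also be few: patients must follow commands and sit unsupported, imminent death is excluded, and all 35 planning patients reached the endpoint.

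**Conclusion.** The point holds in a narrow form. The article fixes an imputation rule and a Kaplan-Meier analysis that make no exception for death before FAC 3. Either way of applying them describes walking as if nobody died. For an assumed 5% to 20% of deaths before FAC 3, the curve at day 60 is about 4 to 16 percentage points too high as a statement of who walks. The true size depends on a death rate that the document does not give, and it is small if deaths are rare. The group test is broadly sound as a test of walking hazards; it becomes misleading if mortality differs by arm or if the result is read as the chance of walking. This is a cheap improvement, not a fault that invalidates the trial.

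**What to change.** Amend the missing-data sentence in the Statistical analysis section to say that:

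- death before FAC 3 is a competing event, and no FAC 3 time is ever imputed for a patient who has died;
- multiple imputation is limited to patients who are alive with unobserved FAC;
- the cumulative incidence of FAC 3 or higher (Aalen-Johansen) is reported by arm beside the death-censored log-rank or Cox comparison, which may remain primary;
- the number of deaths before FAC 3 is given for each arm.

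This should be settled before the data are unblinded. The cost is one extra estimate to explain, and date of death before FAC 3 must be recorded, including after transfer to another hospital. The article does not name date of death among the items it records, so data collection should be checked as well as the analysis wording.

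### Adjusted Cox regression is fitted only if chance baseline imbalance crosses set cut-offs; one pre-specified adjusted model, always fitted, would fix the primary estimate and gain precision

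*Protocol article*

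**What the plan says.** All of this is in the protocol article, Statistical analysis, unless another section is named.

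- The primary objective is addressed by Kaplan-Meier analyses with a comparison of the two groups, under intention to treat. No test is named.
- Adjustment is conditional: "Cox regression analysis will be performed when imbalances between groups are found at baseline in age" (mean difference of 10% or more), MRC sum-score (10% or more), FAC (more than 1) and Charlson index (more than 1). Imbalance is judged by size, not by p-value.
- These variables were selected "as they are potentially related to the primary outcome".
- The trial was sized on a hazard ratio: "In the sample data, we found a hazard ratio of 1.87 at 15 days in favor of BWSTT".
- Randomization and blinding describes variable blocks and states no stratification by a prognostic factor.

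The text leaves three things open: whether a triggered Cox model replaces or accompanies the Kaplan-Meier comparison, whether it contains all four covariates or only the imbalanced ones, and whether the list means any one trigger or all four.

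**The concern.** In a randomized trial, the reason to adjust for a covariate is that it predicts the outcome. The size of the chance imbalance is not the reason. The protocol gives the first reason for its choice of covariates and then makes adjustment depend on the second.

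Two things follow. First, the kind of effect estimate that is reported, unadjusted or covariate-conditional, is settled by chance once the baseline tables by arm are seen. If both analyses are run and disagree, the text does not say which is the primary result. Second, when no trigger fires, baseline information that the trial must collect anyway (the triggers themselves need it) is not used. In a trial of 88 patients without stated stratification, that information could matter.

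**Working it through.** **1. The plan's own sample size.** Inputs: "Given a type 1 error rate of 5% and a power of 0.8", hazard ratio 1.87, 1:1 allocation, 10% dropout, and in the planning data "All patients reached the endpoint within the study period". Sidedness is not stated; two-sided is assumed because one-sided variants give only 64 to 76.

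Schoenfeld events = 4(1.960 + 0.842)² / (ln 1.87)² = 31.40 / 0.3918 = 80.1. Allowing for dropout, 80.1 × 1.1 = 88.1, or 80.1 / 0.9 = 89.0 (90 when rounded to equal arms). Freedman's formula gives 86 without dropout. The stated "required sample size of 88 (44 + 44) patients" is reproduced within rounding. With 10% lost, 88 × 0.9 ≈ 79 events remain, for a power of 79.4%.

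**2. How often the rule fires.** The difference in means has standard error SD × √(2/44) = 0.2132 × SD, so P(trigger) = 2[1 − Φ(cut-off / (0.2132 × SD))]. The protocol gives no SDs, so those below are assumptions, and the covariates are taken as independent.

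Middle case (age 60±15, MRC sum-score 40±10, FAC SD 1, Charlson SD 2):

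| Trigger | Cut-off / SD | z | Probability |
|---|---|---|---|
| Age | 6/15 = 0.40 | 1.88 | 6.1% |
| MRC sum-score | 4/10 = 0.40 | 1.88 | 6.1% |
| FAC | 1/1 = 1.00 | 4.69 | 0.0003% |
| Charlson | 1/2 = 0.50 | 2.35 | 1.9% |

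Any one trigger: 1 − (0.939 × 0.939 × 1.000 × 0.981) = 13%.

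Range over assumed spreads:

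| Spread | CV age | CV MRC | SD FAC | SD Charlson | Any trigger |
|---|---|---|---|---|---|
| Low | 0.20 | 0.15 | 0.5 | 1.5 | 2% |
| High | 0.35 | 0.40 | 1.2 | 3.0 | 45% |

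Even at high spread the FAC trigger fires with probability about 0.01%, so it is close to inert. If all four triggers are needed together, the probability is below 0.0001% throughout.

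**3. Power.** Simulation of 88 patients with 10% random censoring and a covariate-conditional hazard ratio of 1.87. There are four independent standard-normal covariates, each with log-hazard ratio 0.2 to 0.3 per SD. The rule is simulated as: Cox replaces the log-rank test when any trigger fires.

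| Analysis | Power |
|---|---|
| Unadjusted | 60-67% |
| Plan's rule | 63-68% |
| Always adjusted, two covariates | 67-72% |
| Always adjusted, four covariates | 75-77% |

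A separate simulation at 0.3 per SD (3,000 runs, middle spread) gave 59% unadjusted, 60% under the rule and 76% with four covariates. With non-prognostic covariates it gave 79%, 78% and 77%.

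The gap depends on what 1.87 means. A covariate-conditional hazard ratio is attenuated towards 1 when prognostic covariates are left out, and much of the unadjusted shortfall comes from that. If 1.87 is already a marginal hazard ratio, unadjusted power stays near 79% and adjustment adds to it.

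**4. Type I error.** In that simulation (standard error about 0.4 points) it was 4.3-5.3% under the rule, 5.0-5.6% for log-rank and 5.8-6.7% for Cox with four covariates. Other runs put the rule at up to about 6% and the four-covariate model at about 5-7%.

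**The case against.** The strongest defence is that nothing here is invalid. The variables and cut-offs are fixed in advance, only baseline data enter, and p-values are excluded. A reader might infer that data-dependent adjustment produces false positives; the simulations do not support that. This part of the defence stands in full.

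A reader might also infer that the primary test itself switches with the data. The protocol states the Kaplan-Meier comparison without condition and never says that Cox displaces it, so a supplementary role is an equally open reading. What remains is that the text does not settle the role.

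Third, a reader might conclude that the trial is underpowered at about 60-67%. That needs 1.87 to be covariate-conditional. The article says "we found a hazard ratio of 1.87 at 15 days in favor of BWSTT" and mentions no adjustment, so an unadjusted value is the more natural reading. The loss is then an unused gain, not a shortfall against the design. The covariates are also called only potentially related to the outcome, and if they are not prognostic, adjustment costs a little.

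Fourth, the absence of an unconditional hazard ratio could be read as an omission. A condensed article may leave that to the analysis plan, and the wording does not exclude it. The same holds for secondary endpoints. One might suppose that follow-up MRC sum-score will be compared without its baseline value, but the text says only "Between groups comparisons will be made using the appropriate tests according the variable type and distribution" and names no test to correct.

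**Conclusion.** The point holds as an inexpensive improvement and a needed clarification, not as a threat to validity. Adjustment depends on chance imbalance, against the protocol's own reason for choosing the covariates, and the status of a triggered Cox model is undefined.

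The size is conditional. The rule fires in about 2-45% of trials; the 13% middle figure is one point from assumed SDs and should not be quoted alone. Where the covariates are moderately prognostic and 1.87 is conditional, the rule recovers only 1 to 3 points of power over no adjustment, against roughly 10 to 15 points for four covariates always adjusted (67% to 77% and 60% to 75%, pairing the ends of the simulated ranges). Under a marginal 1.87, planned power is kept and the gain is extra. The reproduced sample size of 88 is not in question here.

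**What to change.** Delete the four imbalance triggers. Pre-specify one Cox model of time to FAC 3 or higher, fitted whatever the observed balance, with treatment plus baseline MRC sum-score, age, FAC and Charlson index. Report the hazard ratio with its 95% confidence interval, name it as the primary estimate, and keep the Kaplan-Meier curves with the log-rank test as supportive. Make the change before the data are analysed by arm.

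The change is to wording only: the triggers already require all four covariates at baseline, and the sample size stays at 88. There are two costs. About 2-3 points of power are lost if the covariates turn out not to be prognostic. The Wald test with four covariates is slightly liberal, at about 5-7%. Cutting to two covariates is not a clear remedy: it gave up about half of the power gain, and its type I error in simulation (4.9-6.4%) was much like that with four in the same runs (5.1-6.4%).

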#### Secondary endpoints

The secondary endpoints are walking distance as measured with the 2 Minutes Walking Test (2MWT) [22], muscle strength of upper and lower extremities as measured with the Medical Research Council sum-score (MRC sum-score) [19], perceived exertion after physiotherapy interventions as measured with the Rating of Perceived Exertion scale (RPE scale) [23], physical strain during physiotherapy interventions as measured by peak values of heart rate, mean arterial pressure, respiratory frequency and oxygen saturation, functional mobility as measured with the De Morton Mobility Index (DEMMI) [24, 25], duration of mechanical ventilation, ICU, and hospital length of stay, discharge destination, symptoms of post-traumatic stress as measured with the Posttraumatic Stress Disorder Checklist (PCL-5) [26] and patient satisfaction as measured with a 5-point Likert scale. (Serious) Adverse Events (S) AEs related to the study intervention will be recorded in accordance with good clinical practice guidelines and legislation. Physiotherapy intervention characteristics including numbers of staff and time needed, frequency and content of treatment and walking time, distance and support needed during BWSTT will be recorded for both groups. Outcomes will be assessed at different points in time as is shown in Fig. 2.

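### No baseline adjustment is specified for secondary outcomes, so a plain two-group comparison of the MRC sum-score would give up precision that its recorded baseline value could supply

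*Protocol article*

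**What the plan says.** All of this is in the protocol article.

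- **Rule for secondary outcomes (Statistical analysis).** Outcomes are summarised by mean and SD if normal and by median and IQR if skewed. Then: "Between groups comparisons will be made using the appropriate tests according the variable type and distribution". No test, model or covariate is named.
- **MRC sum-score as an outcome (Secondary endpoints).** The list includes "muscle strength of upper and lower extremities as measured with the Medical Research Council sum-score (MRC sum-score").
- **MRC sum-score at baseline (Statistical analysis).** One of the imbalance checks is "muscle strength (MRC sum-score mean difference ≥ 10" per cent), so the baseline value must be recorded in both arms.
- **The only adjustment described (Statistical analysis).** A Cox regression is run if age, MRC sum-score, FAC or the Charlson index is imbalanced at baseline. The reason given for choosing these variables is "as they are potentially related to the primary outcome".
- **Timing of the other measures (Secondary endpoints).** "Outcomes will be assessed at different points in time as is shown in Fig. 2". That figure is not in the text available for this review.

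**The concern.** The rule selects a test on two criteria, the kind of variable and the shape of its distribution. Coming straight after the choice between mean/SD and median/IQR, it reads as a choice between a t-test and a rank test. Neither uses the patient's starting value.

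For the MRC sum-score that value is in hand. The article already treats baseline strength as potentially prognostic for walking recovery, yet describes no use of it when strength itself is the outcome. The conditional Cox model does not help here, since it is a time-to-event model justified by the primary endpoint.

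What is at stake is the width of the confidence interval for one secondary outcome in a small trial. A chance difference in starting strength would also carry over in part to the follow-up comparison. The randomisation section describes variable blocks and mentions no stratification by strength that would limit such a difference.

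**Working it through.** **1. The plan's own figure.** The article states a "required sample size of 88 (44 + 44) patients before correction for attrition, assuming a 10% dropout rate", and the error rates are "Given a type 1 error rate of 5% and a power of 0.8". Sidedness is not stated; two-sided is assumed. The hazard ratio is 1.87, and all pilot patients reached the endpoint, so events equal patients.

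- Schoenfeld: 4 × (1.960 + 0.842)² / (ln 1.87)² = 80.1, so 81 events. With 10% dropout, 81 / 0.9 = 90 patients.
- Freedman: (1.960 + 0.842)² × (2.87 / 0.87)² = 85.4, so 86 patients without dropout.

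Both are within 2 of 88, so the stated number is reproduced closely. It concerns the primary endpoint only, and nothing below changes it.

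**2. Inputs for the secondary outcome.**

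- From the article: n = 44 per arm.
- Assumed: two-sided 5% test; true difference of 0.5 SD; within-arm correlation r between baseline and follow-up of 0.3, 0.5 or 0.7. The documents give neither the difference nor r.

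**3. Formulas, in SD units.**

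- Standard error: SE = √[(2/n)(1 − r²)], with r = 0 for the unadjusted comparison.
- Power = Φ(0.5/SE − 1.96).
- Difference detectable with 80% power = (1.960 + 0.842) × SE.
- Unadjusted trial of equal precision = 88 / (1 − r²) patients.

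**4. Results at 44 per arm.** The unadjusted SE is √(2/44) = 0.213, so power is Φ(0.5/0.213 − 1.96) = 65%.

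| r | 1 − r² | SE reduction | Detectable difference | Equivalent unadjusted total | Power for 0.5 SD |
|---|---|---|---|---|---|
| unadjusted | 1.00 | none | 0.597 SD | 88 | 65% |
| 0.3 | 0.91 | 4.6% | 0.570 SD | about 97 | 69% |
| 0.5 | 0.75 | 13.4% | 0.517 SD | about 117 | 77% |
| 0.7 | 0.51 | 28.6% | 0.427 SD | about 173 | 91% |

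Estimating one covariate costs a variance factor of about 1 + 1/(88 − 4) = 1.012, which is negligible beside these gains except at low r.

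**5. If about 10% are not analysable.** 44 × 0.9 = 39.6, say 40 per arm. Power is then 61% unadjusted, and 65%, 73% or 88% at r = 0.3, 0.5 or 0.7. The pattern is the same.

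**6. Chance imbalance.** The SE of the baseline difference is also 0.213 SD, and about one trial in three will exceed one SE. An unadjusted comparison carries r times the baseline gap into the follow-up result. For a gap of one SE that is 0.06, 0.11 or 0.15 SD at r = 0.3, 0.5 or 0.7.

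**The case against.** The strongest reply is that the sentence is generic. It names no test, does not call the comparison unadjusted, and does not say whether follow-up values or changes are compared. A condensed article commonly leaves the model for each secondary outcome to the full protocol or the SAP, and neither is shown. Reading the least efficient option into open wording and then criticising it would be unfair. This stands as a limit: plain two-group tests are the most natural reading but remain an inference. It does not dispose of the point, because the article does state a selection rule, and that rule leaves out a measured baseline value.

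The second reply concerns scope, and it also stands. A reader might infer that the secondary outcomes as a class are affected. Among them, a baseline of the same measure is documented only for the MRC sum-score. Length of stay, ventilation duration, discharge destination and satisfaction have none by nature. For the DEMMI, the 2-minute walking test and the PCL-5 it cannot be checked without the schedule figure.

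The third reply is that the gain depends on an unknown correlation and is small at 0.3. That is correct, and is why the range is shown.

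Finally, no power is claimed for any secondary endpoint, so no stated target is missed. That is true, but it is no reason to discard precision that costs nothing.

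**Conclusion.** The point holds as one of efficiency, for one documented secondary outcome. The stated rule specifies no baseline adjustment although the baseline MRC sum-score is collected. The gain forgone is minor at a correlation of 0.3 and material from about 0.5. These figures rest on an assumed 0.5 SD difference, an assumed correlation, a two-sided 5% test and 44 analysed patients per arm.

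A reader might go further and conclude that the planned comparison is biased or has the wrong type 1 error. The documents do not support that. Under randomisation an unadjusted comparison is unbiased over repeated allocations and keeps its error rate, and chance imbalance is already part of its standard error. The carry-over in step 6 of the working describes a single trial conditional on its observed imbalance, and is not a systematic error. The time-to-ambulation analysis is unaffected. The change is worth making, but the trial's main conclusion does not depend on it.

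**What to change.** Keep the present rule for outcomes that have no baseline value, and add before any unblinded analysis:

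*The MRC sum-score, and any other secondary outcome that the assessment schedule shows is measured at baseline, will be compared by ANCOVA of the follow-up value on treatment group and the baseline value of the same measure, whether or not the arms differ at baseline. Robust or bootstrap standard errors will be used if the data are skewed.*

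If an existing SAP already specifies this, confirming it is enough. The cost is one sentence of analysis wording, with no new patients, visits or measurements. Fixing the model in advance also removes a later choice between tests.
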